##### Retention, therapy adherence, medication use, and necessity of continued therapy

Notes will be kept regarding the number of women who are screened for the study, as well as the number who are eligible and consent to participation. Data regarding retention (follow-up rates), participant session attendance, adherence to home programming, pain medication use, and costs will be recorded. The retention goal is to have 100% of participants evaluated for the primary outcomes; an evaluation rate of 90% will be considered acceptable. A home therapy adherence log adapted from Brewer et al. [70] and a pain (prescribed and nonpresecribed) mediation use diary adapted from Van Berge Henegouwen et al. [71] will be reported weekly to interventionists. Data on necessity (yes/no) and frequency of continued therapy following cast removal will also be recorded.

##### Protocol fidelity

The PI will oversee regularly scheduled checks of both our outcome assessors and our interventionists. At each check, the PI will use a protocol checklist to document the number of evaluation and intervention protocol deviations and provide real-time feedback.

##### Blinding

To evaluate the effectiveness of the blind, participants and the evaluator will complete a questionnaire related to their opinion of the allocation at the time of cast removal.

### Statistical analysis

Regarding the continuous primary outcomes (i.e., SF-MPQ, PRWHE) a sample size of 30 per group will give 81% power to identify as significant a mean difference of .75 SD in change in these outcomes between the two groups [72, 73]. A sample size of 30 per group will give 81% power to identify as significant a mean difference of 0.75 SD in change in continuous outcomes between the two groups. A sample size of per group will give 81% power to identify 20% vs. 58% as statistically significant for the Dichotomous outcome, Budapest diagnostic criteria. To adjust to an anticipated dropout rate of 10%, we will overenroll in each group by 3 bringing each group’s enrollment to 33. Following this adjustment, the total sample size will be 66 patients.

Data on recruitment, retention, therapy attendance, medication use, continuance of therapy beyond cast removal, and home program adherence will be expressed in terms of rates (e.g., rate of eligibility and randomization for those screened, rates of retention up to and including the final evaluation, and rates of satisfactory adherence to the intervention protocol). Simple descriptive statistics will be employed. Baseline demographics and characteristics will be summarized and compared between groups using Fisher’s exact test for categorical variables and, depending on whether or not parametric assumptions are met, either a two-sample *t*-test or Mann-Whitney U test for continuous variables.

Continuous variable outcomes (Primary: PRWHE, SF-MPQ; Secondary: Goniometry, grip dynamometry and JPS) will be analyzed using a mixed effects linear models to evaluate change over time between groups. Models will include a random effect to account for the within-subject correlation for repeated measurements, and fixed effects of group, time, and group by time interaction. Model assumptions will be examined before fitting models. If assumptions are not met, nonparametric test (Wilcoxon test) will be used. For dichotomous outcomes (diagnosis of CRPS), Fisher’s exact test will be performed to compare proportions between groups.

In a manner consistent with that described of Walenkamp et al. [73], an achor-based approach to determining the MCID of the PRWHE and SF-MPQ will be taken through use of the Patient’s Global Impression of Change (PGIC) [74] scale as the anchor. The PGIC is a seven-point Likert scale, ranging from ‘very much improved’ to ‘very much worse’, and will be administered at the time of cast removal. The Minimal detectable change (MDC) of these two measures will be determined through use of the statistical methods described by Walencamp et al. [73].

All statistical analyses will be conductedby a PhD biostatistician who will employ the use of the Statistical Analysis System software (SAS, version 9.3, 2011; SAS Institute, Cary, NC). All analyses will be performed on an intent-to-treat basis. Two-sided tests with *p*-value less than 0.05 will be considered statistically significant.

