### Type I complex regional pain syndrome and DRF

Resting pain and pain with activity are common aftereffect following DRF and have been documented to persist in 32.6 and 41.9% of cases respectively at two years post injury [20]. At the time of initial follow up after first definitive medical/surgical treatment of DRF, 81% of persons have been reported to describe having “severe” to “very severe” pain [15].

Type I complex regional pain syndrome (CRPS) is a condition that presents following an injury or illness where nerves are not damaged and is characterized by regional pain, increased sensitivity to touch, swelling, and impairment of motor function that are out out of proportion relative to the extent and location of the original injury/illness [21–24], and has been reported to occur in as many as 37% of persons who sustain DRF [25]. Jellad et al. [25] report that women are 5.8 times more likely than men to develop CRPS after DRF. Persons who sustain low to medium energy impact DRF are 7.7× more likely to develop CRPS than those who sustain high impact fractures, [25]. Additionally, Moseley et al. [26] report that persons with a 0–10 numerical pain scale (NPS) rating of greater than 4 within one week after closed reduction and casting for DRF were 15.1 times more likely to develop CRPS, than those with less than a 5/10 NPS rating.

Many theories exist on the mechanisms for developing Type I CRPS [27]. Recent evidence indicates that CRPS likely has a component mediated by the cerebral cortex [28, 29]. Neuroimaging studies have revealed CRPS-associated shrinkage of the areas of the primary somatosensory cortex (S1 and S2) that represent the painful limb [30, 31]. These cortical changes may be linked with pain sensitization [28, 30]. Other researchers have illustrated disinhibition of the motor cortex and a disrupted body schema in persons with CRPS [32, 33]. Peripheral sensorimotor changes such as those observed by Karagiannopoulos et al. [17] may be indicative of cortical changes occurring following DRF and cast immobilization.

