As many as 37–58% of persons undergoing closed treatment and cast immobilization following DRF go on to develop Type I CRPS [34, 35]. These numbers justify attention, given that most DRF are managed non-surgically via closed reduction and cast immobilization [36, 37]. Therefore, it is important to tailor therapeutic interventions for DRF that address or prevent development of CRPS. Recent evidence suggests that CRPS may develop due to central nervous system changes [27]. Thus, modulation cortical activity might be a noteworthy therapeutic avenue for individuals at risk of developing a CRPS.

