### Rationale for the present study

The upper limb rehabilitation literature is rich in restorative approaches (i.e., resolving impairments when already present). However, little is known about strategies to prevent upper limb, impairment, disability and pain. Recent longitudinal studies indicate that as many as 1/3 to nearly 1/2 of all persons who undergo closed treatment of DRF develop type 1 CRPS [24, 25] and 80% of these patients are women [25]. Current evidence indicates that cortical changes in upper-limb sensory andsensorimotor representation occur within days or weeks during immobilization [46–48], and these changes appear to mimic cortical changes in persons with type I CRPS. A multidimentional MRT, Graded motor imagery (i.e., laterality training, motor imagery and mirror therapy), has emerging support in the literature as a restorative treatment strategy for patients with CRPS [38, 39, 41, 42, 44], however, studies have not examined GMI as a treatment strategy to prevent the onset of CRPS. Implementation of the present protocol will allow investigation into the effects of a modified GMI (mGMI) intervention during the cast immobilization period for women with closed DRF.

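### The 81% power for CRPS is computed correctly but rests on one unexplained control rate at the top of the protocol's own range, and the pain cut-off meant to select high-risk women does not match the evidence cited for it

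*Protocol article*

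**What the plan says.** Three measures are named as primary: the PRWHE, the short-form McGill questionnaire and the Budapest criteria for CRPS. For the last, the Statistical analysis section says the sample size "will give 81% power to identify 20% vs. 58% as statistically significant for the Dichotomous outcome". The number per group is absent from that sentence. The matching sentence for the continuous outcomes reads "a sample size of 30 per group will give 81% power", and the enrolment of 33 per group is built on 30: "To adjust to an anticipated dropout rate of 10%, we will overenroll in each group by 3". The planned test is stated: "For dichotomous outcomes (diagnosis of CRPS), Fisher’s exact test will be performed to compare proportions between groups". No source or reason is given for either rate, and there is no second scenario.

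The protocol gives other figures for the CRPS rate:
- Background, section on type I CRPS and DRF: up to 37% after DRF in general, and for closed treatment with a cast, "As many as 37–58% of persons undergoing closed treatment".
- Rationale: "as many as 1/3 to nearly 1/2 of all persons who undergo closed treatment of DRF develop type 1 CRPS".

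On risk, the same Background section reports that women with a pain "rating of greater than 4 within one week after closed reduction and casting for DRF were 15.1 times more likely" to develop CRPS, the comparison group being those scoring below 5. The Inclusion criteria section says the trial targets people at high risk, requires a pain score above 3 out of 10, and states that the listed factors are strongly associated with CRPS.

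**The concern.** A power statement for a rare or common binary event is only as good as the control rate behind it. Here that rate is the most favourable value the protocol mentions, and the Rationale's range for closed treatment does not reach it. Readers are told 81% and have no way to see how quickly that falls.

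The natural defence of a high control rate is that the trial enrols women selected for risk. The protocol does not make that argument for 58%, and one of the selection criteria departs from its evidence: a woman scoring 4 enters as high risk but belongs to the low-risk comparison group in the cited study.

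Prevention of CRPS is the trial's main rationale. If the true control rate is nearer the lower quoted figures, a non-significant CRPS comparison would be an expected result even with a worthwhile effect, and could be misread as showing that mGMI does not prevent CRPS.

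**Working it through.** **Inputs.** From Statistical analysis: 20% vs 58%, Fisher's exact test, and "Two-sided tests with *p*-value less than 0.05 will be considered statistically significant". Two readings are needed. The number per group is taken as 30, from the continuous-outcome sentence and from 30 + 3 = 33. The arms are not labelled, so 58% is taken as SOC and 20% as mGMI, because benefit is hypothesised for mGMI.

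**Formula.** With n = 30 per group, power is the sum over all 31 × 31 possible tables of Bin(x; 30, p_SOC) × Bin(y; 30, p_mGMI), counting only tables whose two-sided Fisher p-value is below 0.05.

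**The plan's own figure.** At 58% vs 20% the sum is 0.8097, that is 81%. This reproduces the stated power and supports the reading of 30 per group. An uncorrected normal approximation would give 87.5%, so the stated figure agrees with the planned test. After 10% dropout, 33 × 0.90 = 29.7, so the completer number is in order.

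**Other control rates.** The planned effect can be carried over in three ways:
- mGMI rate fixed at 20%.
- Relative risk fixed at 20/58 = 0.345. For example, 0.345 × 50% = 17.2% and 0.345 × 37% = 12.8%.
- Odds ratio fixed at (0.20/0.80)/(0.58/0.42) = 0.25/1.381 = 0.181.

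The midpoint of the Background range is (37 + 58)/2 = 47.5%.

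| SOC rate | mGMI at 20% | Relative risk held (mGMI rate) | Odds ratio held (mGMI rate) |
|---|---|---|---|
| 58% | 81% | 81% (20%) | 81% (20%) |
| 55% | 74% | 77% (19.0%) | 80% (18.1%) |
| 50% | 60% | 70% (17.2%) | 77% (15.3%) |
| 47.5% | 52% | 66% (16.4%) | 75% (14.1%) |
| 37% | 22% | 49% (12.8%) | 63% (9.6%) |
| 33% | 14% | 42% (11.5%) | 57% (8.3%) |

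Holding the absolute difference of 58 − 20 = 38 points would preserve power, but at a 37% control rate it would need an mGMI rate of zero or below.

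**What 81% would take at a 37% control rate.** With 30 per group, the mGMI rate would have to be about 5.5%. Otherwise about 57 per group are needed before dropout at the planned relative risk, or about 123 per group for 37% vs 20%.

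**The pain cut-off.** Side by side, on a 0–10 scale scored in whole numbers:
- Inclusion criteria: above 3, so 4 is eligible.
- Background evidence: high risk is above 4; the comparison group is below 5, so 4 is in the comparison group.

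The two disagree at a score of 4, or between 3 and 5 if fractional scores are allowed. The document does not give the share of women with such scores or their own CRPS risk.

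**Choice of test.** For common rates of 20% to 50%, Fisher's actual type I error here is 2.2% to 2.7%. Boschloo's unconditional exact test uses the same Fisher p-value but rejects up to a critical value of 0.069, with a maximum type I error of 4.7%. Its power is 87% at 58/20 (Fisher 81%) and 67% at 50/20 (Fisher 60%).

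**The case against.** The strongest reply is that 58% lies inside a range the protocol quotes, and that the lower figures describe unselected people. The trial takes women aged 55 or older with low-impact fractures, treated in a cast and in pain. The Background reports CRPS as 5.8 times more likely in women and 7.7 times more likely after low- to medium-energy fractures. This stands in part: enrichment does not rest on pain alone, and a rate above the unselected figures is plausible. But the protocol does not use it to justify 58%, and plausibility does not support showing only the most favourable rate.

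It can also be said that the cut-off mismatch touches only a narrow band of scores, and that the Inclusion criteria cite several sources jointly, one of which might support a score above 3. That is fair. The disagreement between the two sections remains, but its size is unknown.

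Four stronger readings are tempting and not supported:
- That the 81% is an arithmetic error. It is not; it reproduces.
- That the trial will probably miss a real effect. Power falls below one half only for some combinations: with mGMI at 20%, at control rates somewhat below 47.5%; with the relative risk held, only at about 37% and lower; with the odds ratio held, at none of the rates examined.
- That Fisher's conservatism lowers power below the stated value. It is already inside the 81%.
- That counting CRPS at 3 months loses cases that have resolved. The document gives no resolution rate, and counting a diagnosis at any visit would change the quantity estimated without correcting an error.

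**Conclusion.** The point holds as a weakness in the planning assumption, not in the calculation. The CRPS power is 81% only at the ceiling of the protocol's range. At control rates of 50%, 47.5% and 37% it is 60%, 52% and 22% with mGMI at 20%, or 70%, 66% and 49% at the planned relative risk. These figures assume 30 evaluable women per group, 58% as the SOC rate, Fisher's test and a two-sided 5% level.

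Separately, the Background and the Inclusion criteria contradict each other at a pain score of 4. A reader might infer a specific fall in the control rate from this. The document does not support a number, because neither the share of such women nor their risk is given. What can be said is that the mismatch weakens the case for taking the highest rate.

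**What to change.** 1. In Statistical analysis, replace the single CRPS scenario with power over control rates from 37% to 58%. State whether the mGMI rate or the relative risk is held, give the number per group and label the arms. Give the reason for whichever rate is treated as most likely.
2. State that a non-significant CRPS comparison will not be read as evidence that mGMI has no preventive effect, and that the estimate will be reported with its confidence interval.
3. Reconcile the pain cut-off in the Inclusion criteria with the one in the Background, and make the assumed control rate consistent with whichever is intended. Which threshold is right is for the investigators.
4. Optionally, prespecify Boschloo's unconditional exact test in place of Fisher's: 87% vs 81% at 58/20 and 67% vs 60% at 50/20, with type I error still below 5%.

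The cost of items 1 to 3 is mainly wording and a less favourable stated power. If the eligibility rule itself changes, the recruitment estimate (an average of 218 eligible women a year at one clinic, for 66 places) would need checking. Item 4 costs only the use of a less familiar test and must be fixed before the data are seen.

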### Participants

To ensure that criteria for participation are met, patients will be recruited from outpatient clinics staffed by physicians specializing in Orthopaedic, Sports and Family Medicine. The clinics are associated with a large public university in the Midwestern United States. At the time of the first orthopaedic treatment for closed DRF, patients will be offered the opportunity to participate. Prior to enrollment and allocation, oral and written informed consent will be sought. We will seek to enroll 66 participants who have received closed treatment of a distal radius fracture. Through use of a block randomization method, participants will be allocated to a SOC intervention (*n* = 33) group or a SOC + mGMI (*n* = 33) group. Following the consent process, the PI, not a blinded evaluator or interventionist, will actuate the randomization through use of a random block assignment generator [49]. To ensure partcipants are and remain blinded to allotment, participants will be informed that they will be randomized to one of two “occupational therapy treatment approaches” and will be asked not to discuss their treatments with others enrolled in the trial. Evaluators will be blinded to allocation. The feasibility of enrolling these numbers is high given that from 2013 to 2015, the aforementioned Orthopaedics clinic alone cared for an average of 218 women a year who met the below described inclusion criteria. These numbers are likely attributable to the characteristics of the area served by this health system (i.e., urban, northern latitude with slippery weather conditions) which are associated with increased incidence of DRF [7, 9, 10]. The proposed flow of participants from enrollment to completion is reflected in Fig. 1.

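### The primary analyses make inefficient use of baseline pain that the trial already collects: SF-MPQ is compared as a change score, and PRWHE and CRPS are not adjusted at all

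*Protocol article*

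**What the plan says.** The Statistical analysis section assigns PRWHE and SF-MPQ to a linear mixed model of change over time. It describes the within-person part as follows: "Models will include a random effect to account for the within-subject correlation for repeated measurements". The fixed part is "fixed effects of group, time, and group by time interaction". No baseline covariate is listed. CRPS diagnosis by the Budapest criteria is compared between arms by Fisher's exact test, without adjustment.

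Table 2 (Outcome measurements) schedules SF-MPQ at baseline and at all four later visits. PRWHE and the Budapest assessment start only at cast removal. A numerical pain rating above 3/10 within a week of initial management is also an entry condition (Inclusion criteria). The Background subsection on type I CRPS and DRF cites a study in which a rating above 4 in the first week made CRPS 15.1 times more likely.

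The one stated between-arm use of baseline characteristics is descriptive: "Baseline demographics and characteristics will be summarized and compared between groups using" significance tests.

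On size, the plan says that "a sample size of 30 per group will give 81% power to identify as significant a mean difference of .75 SD in change", and for CRPS that a given group size "will give 81% power to identify 20% vs. 58% as statistically significant". Tests are two-sided at 0.05.

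**The concern.** The trial plans for about 30 evaluable women per arm and is powered only for a large effect, 0.75 SD. In that setting a prognostic measurement that is already in the database should be used to reduce variance.

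For SF-MPQ, treating baseline as one more response with a free group effect means that the group-by-time contrast subtracts the whole baseline difference. Subtracting all of it adds noise unless baseline and follow-up are almost perfectly correlated.

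For PRWHE and CRPS nothing is subtracted or adjusted. A chance difference in baseline pain therefore stays in the particular estimate obtained, although it averages out over randomisations. What is at stake is precision and power, and a covariate choice that is better fixed before the data are unblinded than argued about afterwards.

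**Working it through.** **Inputs.** From the Statistical analysis section: 30 per group, effect 0.75 SD of change, two-sided alpha 0.05, stated power 81%. From Table 2: SF-MPQ has a baseline, PRWHE and CRPS do not. Correlations are **assumed**, because the article gives none: 0.3, 0.5 and 0.7 between baseline and follow-up SF-MPQ, and 0.3 to 0.5 between baseline pain and PRWHE.

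**Step 1: the plan's own figures.** A two-sample t-test with 30 per group and a standardised difference of 0.75 has power 81.5% (noncentral t, 58 degrees of freedom). Exact enumeration of Fisher's test for 20% versus 58% with 30 per group gives 81.0%. Both agree with the stated 81%.

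**Step 2: SF-MPQ, change score against baseline adjustment.** With equal SDs at baseline and follow-up, and in units of that SD squared, the per-person variance behind the group contrast is:

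- change score: 2(1 − rho)
- baseline-adjusted: 1 − rho²
- ratio adjusted/change: (1 − rho²) / [2(1 − rho)] = (1 + rho)/2

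The planned effect of 0.75 SD of change then becomes 0.75 / √[(1 + rho)/2] on the adjusted scale.

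| Assumed rho | Change | Adjusted | Ratio | SE reduction | Standardised effect | Power, 30 per group |
|---|---|---|---|---|---|---|
| 0.3 | 1.40 | 0.91 | 0.65 | 19% | 0.93 | 94% |
| 0.5 | 1.00 | 0.75 | 0.75 | 13% | 0.87 | 91% |
| 0.7 | 0.60 | 0.51 | 0.85 | 8% | 0.81 | 87% |

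The direction does not depend on equal SDs. With SDs s0 and s1, the change variance is s0² + s1² − 2·rho·s0·s1 = s1²(1 − rho²) + (s0 − rho·s1)², which is never below the adjusted variance.

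**Step 3: PRWHE with baseline pain as covariate.** With no baseline PRWHE, the comparison at a visit has relative variance 1 unadjusted and 1 − r² adjusted. Reading the planned effect as 0.75 SD of PRWHE at that visit (an assumption, since change from baseline is not available for this outcome):

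- r = 0.3: variance 0.91, SE 5% smaller, effect 0.75/√0.91 = 0.79, power about 85%
- r = 0.5: variance 0.75, SE 13% smaller, effect 0.75/√0.75 = 0.87, power about 91%

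**Step 4: how often chance imbalance arises.** The SE of the difference in baseline means is √(2/30) = 0.258 SD. A difference of at least 0.25 SD in either direction has probability 2[1 − Φ(0.25/0.258)], about 33%. At r = 0.5 such a difference moves the unadjusted PRWHE estimate by 0.5 × 0.25 = 0.125 SD, one sixth of the planned 0.75 SD.

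These are large-sample variances with 58 degrees of freedom kept throughout. They ignore the small cost of estimating the covariate's slope, so the gains are slightly optimistic. No gain is calculated for CRPS, because the article does not give the strength of the association within the eligible pain range.

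**The case against.** The strongest reply is that nothing planned fails. Randomisation makes the unadjusted analyses unbiased, Fisher's test is valid, and the stated power reproduces. That stands, and it limits the point to efficiency.

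Several stronger readings are tempting, but the article does not support them.

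- *That no primary analysis takes account of baseline pain.* This is not so for SF-MPQ, whose baseline is modelled and subtracted by the group-by-time contrast. The loss there is only that of change score against covariate adjustment.
- *That ignoring a 15-fold risk factor is serious for CRPS.* The cited contrast is a rating above 4 against one below 5, and entry already requires more than 3. On a whole-number scale only women scoring exactly 4 remain in the lower-risk group, so much of that contrast is removed by eligibility.
- *That one random effect forces equal correlation between all visits and inflates the test size.* That follows only for a random intercept with independent residuals. It is the natural reading, but neither the type of random effect nor the residual covariance is stated, and such detail is commonly left to an analysis plan. A size of about 11% to 15% appears only under an assumed exponential decay (3-week correlation 0.7 to 0.9), for the most extreme contrast, baseline to 12 weeks after a six-week cast. Under the same assumptions it is about 7% at 4 weeks after cast removal, where the pain hypothesis is placed; the week-3 test is conservative; and under equal correlation the size is about 5%. With no correlations in the article, this is not a finding. PRWHE and CRPS have no baseline-to-late contrast in any case.
- *That the baseline significance tests do harm.* They are uninformative in a randomised trial, but they drive no analysis and removing them changes no result.

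**Conclusion.** The point holds as a matter of lost precision. At the assumed correlations, the planned SF-MPQ contrast has 1/0.85 = 1.18 to 1/0.65 = 1.54 times the variance of a baseline-adjusted one, and adjustment would lift power from 81.5% to between 87% and 94%. PRWHE would gain less at weak correlation: about 85% at 0.3, and 91% at 0.5. For CRPS the gain cannot be sized from the article.

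The SF-MPQ advantage holds at every correlation below 1 when the SDs are equal; its size depends on the assumed value. The PRWHE gain depends on baseline pain predicting PRWHE, which is plausible but not quantified. The point shows no bias, no invalid test and no error in the sample size.

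**What to change.** - **SF-MPQ:** use the four post-baseline visits as responses, with baseline SF-MPQ and its interaction with visit as covariates. Alternatively, keep baseline as a response and constrain its mean to be equal across arms. Name the visit at which the group difference is read.
- **PRWHE:** add baseline SF-MPQ or the entry pain rating, with its interaction with visit, and report the group difference at a named visit. A covariate with a constant coefficient cancels out of a within-person change between visits, so it would not help a contrast of that kind.
- **CRPS:** keep Fisher's exact test and, optionally, report beside it a risk difference adjusted for baseline pain. At the planning rates, 30 × 0.20 + 30 × 0.58 is about 23 events, so keep to a single covariate.

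Fix the choice of baseline pain measure before unblinding. The cost is a few lines of analysis text and code, with no new visits, participants or data.

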### Function and impairment following DRF

Women sustaining a wrist fracture are likely to have a clinically important functional decline in self care, productivity, and leisure performance [14]. Disability levels based on the Patient Rated Wrist and Hand Evaluation (PRWHE) are reported to be high (75%) at the first week after DRF, and modertate (43%) at 8 weeks post injury [15]. Wrist and forearm active range of motion (AROM) and hand grip strength are the most commonly assessed physical impairments in all persons who are status-post DRF and are, on average, reduced by 40 to 50% at eight weeks post injury [16]. A case-control designed study revealed that distal radius fractures in both men and women have large effects (ƞ^*2*^ = .49) on grip strength relative to matched controls [17] and, in turn, grip strength is a significant predictor of wrist function as measured by the PRWHE [18, 19]. Recent research also suggests that persons with DRF experience significant impairments in sensorimotor functions such as wrist joint proprioception and moving light touch awareness [17]. There are also indications that sensorimotor functions have significant associations (fine motor: *r* = −.52, joint position sense error: *r* = .63) with pain levels [17].

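### A check made before fitting can replace the mixed model for both continuous primary outcomes with a single Wilcoxon test, which drops the repeated visits and does not match the stated power basis

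*Protocol article*

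**What the plan says.** In the protocol article, Statistical analysis, the continuous outcomes (PRWHE and SF-MPQ as primary; goniometry, grip and joint position sense as secondary) "will be analyzed using a mixed effects linear models to evaluate change over time between groups". The model has a random effect for the woman and "fixed effects of group, time, and group by time interaction".

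Two sentences then set a contingency: "Model assumptions will be examined before fitting models. If assumptions are not met, nonparametric test (Wilcoxon test) will be used". The article does not say which Wilcoxon test is meant, at which visit, or whether it is applied to scores or to change.

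The same section states 81% power with 30 women per group for a difference of 0.75 SD in change. It ends with the statement "All analyses will be performed on an intent-to-treat basis".

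Two other places matter. The Hypothesis places the expected effect on disability and pain at 1 month after cast removal. Table 2 schedules SF-MPQ at five time points including baseline, but PRWHE at only three: cast removal, 4 weeks and 12 weeks.

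**The concern.** This is a stated replacement rule for two of the three primary outcomes, not a detail left open.

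- **The trigger comes at the wrong moment.** The mixed model makes no normality claim about raw scores taken together. It makes one about the random effects and residuals, which are estimated by the fit. A decision taken beforehand can discard a model whose assumptions would have been acceptable.
- **The replacement is a smaller analysis.** Properly applied, a Wilcoxon test makes one two-sample or one paired comparison. It cannot represent five SF-MPQ or three PRWHE visits, has no group-by-time term, and excludes a woman without the chosen visit. The mixed model would keep her other visits, which fits the intent-to-treat statement better.
- **The power statement is tied to change.** A rank-sum test on scores at one visit ignores the SF-MPQ baseline, so its power is not the stated 81% except by coincidence.

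At stake is whether the main result for pain and function comes from the planned model or from a test with different power and a different target, chosen after the data have been looked at.

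**Working it through.** **Inputs from the article.** 30 evaluable per group; 0.75 SD difference in change; two-sided 0.05; SF-MPQ with a baseline; PRWHE without one.

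**Assumed, because the article gives no value.** Correlation ρ between baseline and follow-up; equal SD σ at both times; normal data; no group difference at baseline.

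**Step 1, the plan's own figure.** Two-sample t-test, n = 30 per group, d = 0.75: power 81.5%. The stated 81% reproduces and is not in dispute.

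**Step 2, effect on the visit score.** SD of change = σ√(2(1 − ρ)). A difference of 0.75 SD of change is therefore, in units of the SD of the visit score, d = 0.75 × √(2(1 − ρ)). For example, at ρ = 0.7, d = 0.75 × √0.6 = 0.58; at ρ = 0.2, d = 0.75 × √1.6 = 0.95.

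**Step 3, power for SF-MPQ at 4 weeks after cast removal** (20,000 simulated trials per row):

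| ρ | d on visit score | Rank-sum on visit score | Rank-sum on change | t-test on change |
|---|---|---|---|---|
| 0.2 | 0.95 | 94% | 79% | 82% |
| 0.3 | 0.89 | 90% | 79% | 81% |
| 0.4 | 0.82 | 86% | 79% | 81% |
| 0.5 | 0.75 | 79% | 79% | 81% |
| 0.6 | 0.67 | 70% | 79% | 82% |
| 0.7 | 0.58 | 57% | 79% | 82% |
| 0.8 | 0.47 | 42% | 79% | 81% |

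Other runs of the t-test on change gave up to 83%. The visit-score test has more power than the t-test on change at ρ of 0.4 or below, about the same at 0.5, and clearly less from 0.6 upward.

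**Step 4, one visit against all visits.** Three visits, ρ = 0.5, and a 0.75 SD difference at the middle visit only: the group-by-time test rejects in 85% of trials, and a rank-sum test at the last visit in 5%. The answer depends on which single visit the fallback uses.

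**Step 5, PRWHE.** All three PRWHE visits fall at or after cast removal. Suppose a benefit of 0.75 SD is present at cast removal and persists unchanged. Every group-by-time contrast is then zero. Simulated at ρ = 0.5 and 0.7:

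- group-by-time test: about 5% rejection, its nominal error rate;
- rank-sum test between groups at 4 weeks: 79%;
- t-test between groups at 4 weeks: 82%.

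So for PRWHE the remedy cannot simply be to insist on the interaction.

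**The case against.** The strongest defence is that the hypothesis concerns an effect at 1 month after cast removal. A between-group rank-sum test at that visit is a valid randomised comparison that addresses it. The article never names the interaction as the deciding test, and for PRWHE the interaction would miss a steady benefit that the rank-sum test detects (Step 5). This stands. A reader might infer that the fallback always tests the wrong hypothesis or always loses power; neither is supported. Step 3 shows a gain at low correlation, and a rank-sum test on change costs only about 2 points.

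A reader might also infer loss of error control, by taking Wilcoxon to mean a signed-rank test within one arm, or by pooling all visits as if independent. The surrounding text is about comparisons between groups, and pooling is mentioned nowhere, so neither reading is favoured. That the section calls its baseline rank test Mann-Whitney U is too thin a basis for the first.

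Nor does the article show that the fallback is the likely route. It names no normality test and does not say that pooled raw scores would be examined.

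Finally, a condensed article may leave the form of the test, the visit and the trigger criterion to an analysis plan. That is fair, and their absence is not the point here. The timing of the check and the replacement of the repeated-measures model by a Wilcoxon test are both written down. With 10% dropout anticipated, the loss of women missing one visit would be modest.

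**Conclusion.** The point holds as a flaw in a stated rule. The check is placed before the quantities it concerns exist, and failing it replaces a repeated-measures analysis with a single comparison that discards visits, incompletely observed women and, if applied to SF-MPQ visit scores, the baseline.

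The effect on SF-MPQ power can go either way: from about 94% at ρ = 0.2 to 42% at ρ = 0.8, against 81 to 83% for the t-test on change. These figures rest on assumed correlations, equal variances and normal data. The structural mismatch does not depend on them. The stated 81% is correct for what it describes, but does not describe a rank test on visit scores.

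The article does not support a claim that error rates are lost or that the switch will probably happen. It is worth correcting because the change is cheap and affects two primary outcomes.

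**What to change.** Replace the two sentences on assumptions and the Wilcoxon test with wording such as:

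> The mixed model is the primary analysis of PRWHE and SF-MPQ. Residuals will be examined after fitting; if they depart clearly from normality, the same model-based contrasts will be reported with a participant-level bootstrap or a small-sample-corrected robust standard error.

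Name the contrast at 4 weeks after cast removal for each outcome:

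- **SF-MPQ:** the between-group difference in change from baseline.
- **PRWHE:** the model-estimated between-group difference at that visit, not the group-by-time interaction, because Table 2 has no PRWHE before cast removal.

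If a rank analysis is wanted, keep it as a sensitivity analysis only: a rank-sum test between groups on SF-MPQ change, or on the 4-week PRWHE score.

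The cost is a wording change and a few lines of code, with no extra patients or visits. The downside is slightly wider intervals when the bootstrap or robust standard error is used.
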